### Randomization and Blinding

This study uses a randomized block design with a block length of 4. Random numbers for grouping were generated using Stata (version 18.0; StataCorp). A dedicated researcher, who will not participate in the recruitment of participants or data collection, will oversee the random grouping process, thereby ensuring that the grouping decisions remain independent of actual operations. Before the initiation of the study, personnel not involved in participant recruitment or data collection will create an allocation table based on the random number sequence and maintain this table in strict confidentiality to prevent any potential leaks. Group allocations will be concealed within sealed, opaque envelopes, which the researcher will open before the intervention to access the allocation plan for each patient.

Given the overt nature of acupoint massage and external mirabilite application, blinding of participants, their guardians, and the health care providers administering the interventions was not feasible. This represents an inherent methodological limitation of this study. To mitigate potential measurement bias due to the lack of blinding, we implemented several procedural strategies. A strict and standardized outcome assessment protocol was established, wherein independent assessors, specifically nurses who were blinded to group allocation, evaluated patients at 4-hour intervals. These evaluations were conducted through direct auscultation of bowel sounds combined with patient or parental reporting. Documentation of first flatus or defecation requires both active bowel sounds and clear verbal confirmation, thereby reducing sole reliance on subjective reporting. Researchers responsible for data collection and statistical analysis remained blinded to group assignment and accessed only deidentified datasets to maintain analytic independence. Furthermore, throughout the informed consent process and study duration, families received standardized, neutral communication, emphasizing that the study aimed to compare different postoperative care approaches, avoiding implications of differential efficacy to reduce expectation bias. All outcomes were recorded on structured case report forms (CRFs), mandating concurrent documentation of objective signs, such as auscultation findings, alongside the reporting source.

### Interventions

#### Conventional Care Group

The children will receive standard postoperative care, including monitoring of vital signs, necessary medication, as-needed pain relief, dietary adjustments, and rehabilitation training, but will not undergo acupoint massage or the external application of mirabilite nor will any investigational interventions be administered.

#### Acupoint Massage Group

On the basis of conventional care, standardized acupoint massage will be performed by certified physicians and nurses to promote the recovery of organ function and alleviate symptoms of gastrointestinal dysfunction. The selected acupoints include Zusanli (bilateral; ST-36), Tianshu (bilateral; ST-25), Zhongwan (CV-12), and Neiguan (PC-6), which are informed by pertinent studies on the recovery of gastrointestinal function following laparoscopic surgery and adhere strictly to the “World Health Organization Standard Acupuncture Point Localization” [24,25]. Each acupuncture point will receive a combination of kneading and pressure techniques at a frequency of 30 repetitions per minute, with a pressure depth ranging from 0.5 to 1 cm, sustained for a duration of 2 minutes, and administered twice daily. The applied pressure must remain within a tolerable range for the child, ensuring that the skin becomes slightly reddened without eliciting pain. The child’s abdominal wound will be assessed before the procedure to avoid the puncture site.

#### Mirabilite Group

On the basis of conventional care, an external application of mirabilite will be administered to the abdomen, drawing on relevant studies concerning acute pancreatitis [26]. Preparation entails grinding medical-grade mirabilite into a powder, which is then mixed with warm water in a 1:1 ratio to create a paste. This paste will be evenly spread onto gauze to a thickness of approximately 0.5 cm and placed over the area surrounding the navel, extending from above the xiphoid process to below the pubic symphysis. The gauze will be anchored with breathable tape to prevent pressure on the drainage tube, while a constant temperature heating pack will maintain warmth during the application. Each application will last for 1 hour, administered twice daily. Skin reactions will be closely monitored, and the application will be discontinued immediately if redness or allergic reactions occur.

#### Combination Group

This group will simultaneously receive both acupoint massage and external application of mirabilite, adhering to the same protocols as the single-intervention groups, but spaced apart from each other. An interval of at least 1 hour will be maintained between the 2 interventions to avoid interference. The acupoint massage will promote the smooth flow of Qi and blood within the meridians, while the localized stimulation from the external application of mirabilite will further facilitate the recovery of gastrointestinal function and enhance therapeutic effects.

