	**Safety monitoring**														
		Skin irritation									✓			✓	
		Massage tolerance									✓			✓	

**Table 2 table2:** Intervention program.

Group	Intervention components	Frequency or duration	Key operational parameters	Safety monitoring
Acupoint massage	Stimulation of Zhongwan (CV-12), Tianshu (bilateral; ST-25), Zusanli (bilateral; ST-36), and Neiguan (bilateral; PC-6)	Twice daily (2 minutes per acupoint)	Technique: rotatory kneading+vertical pressing Pressure: ≤0.5 kg (aged 2-5 y) and ≤1 kg (aged 6-12 y) Sequence: CV-12→ST-25→ST-36→PC-6	Preprocedure wound assessment Real-time tolerance monitoring Skin response check Emergency stop for vomiting or pain
Mirabilite application	Periumbilical paste application (xiphoid process to pubic symphysis)	Twice daily (1 hour, with a 5-minute margin on either side)	Allergy test Preparation: 1:1 mirabilite: water (36 °C-38 °C) Thickness: 0.5 cm uniform layer Fixation: hypoallergenic tape Constant temperature heating pack	Preapplication skin test Temperature monitoring (36 °C-38 °C; ΔT≤1 °C) Visual inspection Discontinuation for erythema or blisters
Combination group	Both interventions	Massage: 2 per day; mirabilite: 2 per day; minimum interval: 60 minutes	Sequence: massage→mirabilite (preferred) Prohibited: massage within 1 hour after mirabilite application Separate documentation for both	Combined monitoring of both interventions

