#### Secondary Outcomes

##### Overview

To comprehensively evaluate postoperative recovery and investigate potential mechanisms, the subsequently mentioned secondary outcomes will be monitored. The first outcome is the incidence of PONV. The frequency of PONV episodes will be recorded every 4 hours. The second outcome is postoperative inflammatory markers. To establish baseline values and track the perioperative inflammatory trajectory, venous blood samples for quantification of WBC count and serum amylase levels will be collected before surgery, at 3 hours after surgery, and on the morning of postoperative day 1. These parameters will serve to assess pancreatic functional recovery, screen for complications, and gauge the magnitude of the systemic inflammatory response. Furthermore, they will provide indirect indicators of gastrointestinal functional status, offering valuable reference data for monitoring postoperative clinical progression.

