##### Data Collection and Management

Data collection will be conducted by trained, blinded researchers. Baseline data will be collected after the children have completed random allocation and before the initiation of the first intervention. Data will be meticulously recorded during each acupoint massage session and the application of mirabilite, which includes specific time points of the intervention, actual duration of execution, selected acupoints for acupressure, intensity of techniques, site of mirabilite application, and the child’s tolerance and compliance with the intervention. Core observational indicators for postoperative recovery will be collected strictly, with the times of first flatus and first bowel movement recorded through scheduled inquiries by medical staff to the child or family, validated through physical examinations, and accurately documented. Instances of PONV will also be recorded, while inflammatory indicators will be documented at 3 hours after surgery and the following morning.

All collected data will be recorded using standardized paper CRFs. All paper CRFs will be securely stored by the principal investigator, and data entry will follow a double-entry system. An electronic database will be established using Microsoft Excel, with regular checks to identify potential errors or outliers. Source data verification will be performed regularly, comparing CRF data with original medical records to ensure transcription accuracy.

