### Data Analysis

Statistical analyses will be performed using SPSS (version 25.0; IBM Corp) and RStudio (Posit PBC), incorporating the *survival* package. A 2-sided significance level of .05 will be applied for all tests, and an intention-to-treat analysis will be implemented to handle missing data.

Categorical baseline variables will be summarized as frequencies and percentages, with group comparisons conducted using chi-square tests or Fisher exact tests as appropriate. Continuous variables will be described as mean with SD if normally distributed and compared via 1-way ANOVA; nonnormally distributed variables will be presented as median with IQR and compared using the Kruskal-Wallis *H* test. Time-to-event analysis will be applied to the primary outcomes, namely time to first flatus and time to first defecation. Cumulative event rates will be visualized using Kaplan-Meier curves, and overall, between-group differences will be assessed via the log-rank test. To address multiple comparisons, a prespecified hierarchical contrast approach will be used. Primary contrasts, including each intervention group compared to the routine care group, will be evaluated using a Bonferroni-adjusted significance threshold of .0167. Exploratory pairwise contrasts between the combination group and each monotherapy group will be conducted only if significant differences are observed in the primary contrasts. Additionally, a Cox proportional hazards regression model will be used to estimate adjusted hazard ratios with 95% CIs for each intervention relative to routine care while controlling for baseline covariates identified in univariable analysis with a *P* value of <.10.

The secondary outcome analysis will include comparisons of PONV incidence using chi-square tests, with Bonferroni-adjusted pairwise testing where applicable. Inflammatory markers, including WBC count and serum amylase, will be analyzed using repeated-measures ANOVA to evaluate changes at 3 hours after surgery and on the morning of postoperative day 1. Safety outcomes will be summarized descriptively, and between-group differences in adverse events will be examined using chi-square or Fisher exact tests.

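### The 3-hour WBC count and amylase follow short, possibly arm-dependent exposure, yet are tested together with day 1; a day-1 comparison adjusted for the pre-surgery value would be the safer main marker analysis

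*Protocol article*

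**What the plan says.** Table 1 places randomization and all study interventions after surgery. Data Collection and Management adds the order: "Baseline data will be collected after the children have completed random allocation and before the initiation of the first intervention". No clock time for the first session is given.

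For the combination group, the text requires that "An interval of at least 1 hour will be maintained between the 2 interventions to avoid interference", and Table 2 has "Massage: 2 per day; mirabilite: 2 per day; minimum interval: 60 minutes", with massage before mirabilite as the preferred order. Massage lasts 2 minutes per acupoint, and a mirabilite application lasts 1 hour with a 5-minute margin. A skin test comes before application; its timing and duration are not stated.

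Under Secondary Outcomes (Overview), the blood samples "will be collected before surgery, at 3 hours after surgery, and on the morning of postoperative day 1". Their stated purposes are to set baseline values, follow the inflammatory course and screen for complications. Data Analysis says that the markers "will be analyzed using repeated-measures ANOVA to evaluate changes at 3 hours after surgery and on the morning of postoperative day 1". It does not say what role the pre-surgery value plays, or whether the group main effect or the group-by-time term carries the comparison.

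**The concern.** The 3-hour draw is timed from surgery, so the treatment a child has had by then depends on when the first session began. Two full combination rounds cannot fit into 3 hours. In the single-intervention arms, a twice-daily schedule spread over the day also allows at most one session. Exposure at this draw is therefore short. It can also differ by arm, and it is most easily incomplete in the combination group, which the Introduction expects to do best.

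The ANOVA nevertheless gives the 3-hour value the same standing as day 1. If treatment has had little effect by 3 hours, a group effect taken over both times is weakened. If part of the effect is already there, the group-by-time term is weakened instead. At stake is the evidence on anti-inflammatory action that the Discussion hopes to draw from these markers. These are secondary outcomes; the primary outcomes are not affected.

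**Working it through.** **1. Plan's own figure.** The plan states no power or effect size for the markers, so there is none to reproduce. The arm size used below is the planned 72 / 4 = 18.

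**2. Length of one combination round** (Table 2 and the Combination Group text).
- Massage: 4 named points × 2 = 8 min, or 7 sites (three points bilateral) × 2 = 14 min.
- Gap: at least 60 min. Mirabilite: 60 min.
- Total: 8 + 60 + 60 = 128 min, or 14 + 60 + 60 = 134 min.
- With a 55 to 65 min application: 123 to 139 min. If 5 minutes are added both before and after: 14 + 60 + 70 = 144 min.

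**3. Latest massage start for a complete round by 180 min.** 180 − 134 = 46 and 180 − 128 = 52 min after surgery. Across all readings the range is 180 − 144 = 36 to 180 − 123 = 57 min. Two rounds need at least 2 × 123 = 246 min, more than 180.

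**4. Exposure for later starts, massage first.** Mirabilite begins 68 to 74 min after massage starts.

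| Massage start after surgery | Mirabilite received by 3 h |
|---|---|
| 60 min | 46 to 52 of 60 min |
| 90 min | 16 to 22 min |
| 106 to 112 min or later | none |

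By comparison, massage alone is finished by 3 hours if started by 166 to 172 min (180 − 14, 180 − 8), and a 60-minute mirabilite application if started by 120 min.

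**5. Power.** These inputs are assumptions, because the article gives no marker effect or variance: day-1 effects 0, 0.5, 0.5 and 1.0 SD; 18 per arm; the same correlation ρ between all three times; a share s of the day-1 effect present at 3 hours; one overall four-arm F test at 0.05. The squared deviations from the mean effect of 0.5 sum to 0.25 + 0 + 0 + 0.25 = 0.5, so the noncentrality for unadjusted day 1 is 18 × 0.5 = 9. The others are:
- group main effect: 9 × ((1 + s)/2)² / ((1 + ρ)/2)
- group-by-time: 9 × (1 − s)² / (2(1 − ρ))
- day 1 adjusted for the pre-surgery value: 9 / (1 − ρ²)

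Example at ρ = 0.5, s = 0: 9 × 0.25/0.75 = 3.0; 9/1 = 9.0; 9/0.75 = 12.0.

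Power at ρ = 0.3 / 0.5 / 0.7 from the noncentral F:

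| Share at 3 h | Group effect | Group-by-time | Day 1 unadjusted | Day 1 adjusted |
|---|---|---|---|---|
| 0 | 0.30 / 0.26 / 0.23 | 0.52 / 0.68 / 0.90 | 0.68 | 0.73 / 0.82 / 0.94 |
| 25% | 0.45 / 0.39 / 0.35 | 0.31 / 0.42 / 0.65 | 0.68 | same |
| 50% | 0.61 / 0.55 / 0.49 | 0.15 / 0.20 / 0.32 | 0.68 | same |
| 100% | 0.87 / 0.82 / 0.76 | 0.05 | 0.68 | same |

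A simulation of 10,000 trials per correlation gave 0.72, 0.81 and 0.94 for the adjusted day-1 test, in agreement with the formula.

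**The case against.** The strongest reply is that everything turns on a first-session time the article does not give and may well have left to the intervention manual in Multimedia Appendix 1, which is not shown. That stands. A reader might infer that a combination round can hardly be completed by 3 hours, or that the 3-hour value is largely pre-treatment. The documents support neither. One round fits with about 46 to 52 minutes to spare, screening and consent are placed at enrollment, and the skin test is not placed after surgery. In the preferred order the massage part is finished for any start up to about 166 minutes.

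A reader might also infer that the planned analysis simply averages the two times. That is true only of the group main effect. The stated aim of evaluating changes fits group-by-time at least as well, and a 3-hour value free of any effect then acts as a baseline. Against unadjusted day 1, that term with no early effect loses 16 points at ρ = 0.3 (0.68 − 0.52), loses none at 0.5 and gains 22 at 0.7 (0.90 − 0.68). So part of the advantage of adjusted day 1 comes from the baseline adjustment and not from setting the 3-hour value aside. Like for like, the group effect loses about 38 to 45 points with no early effect and 7 to 19 points with half the effect present. Naming the tested term could be left to an analysis plan; the point does not rest on that omission.

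Nor does a chance arm difference at 3 hours amount to bias, since the test's significance level covers it.

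What the reply does not remove is that neither reading is robust. The group effect does badly when little effect is present at 3 hours, and group-by-time does badly when part of it is. The article gives no basis for knowing which case applies.

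**Conclusion.** The point holds as a cheap improvement to a secondary analysis. The article establishes that the 3-hour sample is tied to surgery, that it follows at most one combination round, that exposure by then can differ between arms, and that this value is tested together with day 1. It does not establish that exposure was in fact incomplete. Reading twice daily as spread over the day is an assumption for the single-intervention arms.

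Under the stated assumptions, with 0 to 50% of the effect present at 3 hours, day 1 adjusted for the pre-surgery value (0.73 to 0.94) has higher power than the group main effect (0.23 to 0.61) or group-by-time (0.15 to 0.90) in every combination examined. The advantage has a limit. If the full effect were already present at 3 hours, the two-time average (0.76 to 0.87) would beat unadjusted day 1 (0.68) throughout. It would also match or beat adjusted day 1 at ρ of 0.5 or less, though not at 0.7, where the comparison is 0.76 against 0.94.

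The figures do not justify barring the 3-hour value from all testing; that would be a preference.

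**What to change.** In Data Analysis, prespecify the between-arm comparison of day-1 morning WBC count and amylase, adjusted for the pre-surgery value, as the main marker analysis. This can be an ANCOVA or the day-1 contrast from a baseline-adjusted repeated-measures model. Keep the 3-hour comparison as a supportive early value. From the session times that Data Collection and Management already has recorded, report by arm how many children had completed a session before the 3-hour draw.

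The cost is a change of wording: no new samples or visits, and no change to treatment or sampling times. The Results section reports that no interim analysis has been done, so this can still be prespecified. The downside is that an early effect at 3 hours gets less weight.

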### Outcome Measures

#### General Sociodemographic Data

To characterize the study population and assess potential confounding factors, we will collect basic demographic and clinical information from pediatric patients before the intervention, including age, gender, height, weight, and BMI, as well as disease diagnosis, specific indications for undergoing ERCP, history of abdominal surgeries, comorbidities, relevant family medical history, the number of previous ERCP procedures, guardians’ educational level, annual family income and the type of residence (urban or rural). Annual family income will be categorized as: <CNY ¥50,000 (US $7183), CNY ¥50,000-100,000 (US $7183-14,366), CNY ¥100,000-200,000 (US $14,366-28,731), and >CNY ¥200,000 (US $28,731).

#### Primary Outcomes

The primary objective of this study is to investigate the speed of gastrointestinal function recovery in pediatric patients following ERCP. The core indicators include recording and comparing the time until the first passage of gas and the time until the first bowel movement after surgery between the 2 patient groups. Assessments will be performed every 4 hours by trained nursing staff through direct inquiry of the child or guardian, combined with auscultation of bowel sounds, to objectively validate the occurrence of flatus or defecation. These 2 time points serve as critical objective markers that reflect the recovery of gastrointestinal motility.

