**Methods:**

A single-center, single-blind, randomized controlled trial will be conducted involving 72 children aged between 2 and 12 years who have undergone ERCP. Participants will be randomly allocated to 1 of the 4 groups: acupoint massage group (stimulating ST-36, ST-25, CV-12, and PC-6 for 2 minutes per point; twice daily), mirabilite group (abdominal application for 1 hour; twice daily), combination group (both interventions; at least 1 hour apart), or conventional care group. The primary outcome is the time to first postoperative flatus and defecation. The secondary outcomes include the frequency of postoperative nausea and vomiting and inflammatory markers. Data will be analyzed using intention-to-treat analysis with SPSS, using ANOVA, chi-square, and nonparametric tests as appropriate.

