**Figure 1 figure1:**
[figure not shown]
Flow diagram of the study design. PONV: postoperative nausea and vomiting; WBC: white blood cell.

**Table 1 table1:** Clinical trial procedure.

Study period						Enrollment			Baseline (before surgery)			Intervention and assessment (after surgery)			Closeout (discharge)

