**Enrollment**															
	Eligibility screen					✓									
	Informed consent					✓									
	Randomization											✓			

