### Participants

Participants will be recruited from children who have undergone ERCP in the pediatric department of Shanghai Shuguang Hospital. Inclusion criteria are as follows: (1) aged between 2 and 12 years, (2) having completed ERCP, (3) deemed suitable for pediatric acupressure and external mirabilite application, (4) having provided written informed consent by legal guardians, and (5) having provided age-appropriate assent from the child. Exclusion criteria are as follows: (1) history of abdominal surgery or severe gastrointestinal dysmotility; (2) concomitant failure of vital organs, such as the heart, lung, or kidney; (3) known allergy to mirabilite or skin lesions contraindicating topical application; (4) cognitive or behavioral impairment that would compromise cooperation with acupressure; and (5) intraoperative conversion to open surgery due to major complications, such as perforation or severe bleeding. Participants will be withdrawn under the following circumstances: (1) voluntary withdrawal by the child or their parent; (2) loss of communication during the intervention that precludes further assessment; or (3) the occurrence of a serious adverse event, including marked clinical deterioration or an acute medical condition.

Eligible children will be identified through an electronic medical record system, with 2 senior physicians independently evaluating their enrollment criteria. In the event of disagreement, a third expert will adjudicate. All participants will have the research protocol thoroughly explained by a dedicated research nurse before surgery, and informed consent will be obtained from the guardians and the children.

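### Primary times run from surgery but randomisation follows ERCP, and no rule keeps flatus or stool passed before randomisation from counting as a primary event

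*Protocol article*

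**What the plan says.** **Time origin.** Under Primary Outcomes the core indicators include "recording and comparing the time until the first passage of gas and the time until the first bowel movement after surgery". The abstract uses the same origin: "The primary outcome is the time to first postoperative flatus and defecation".

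**When children are randomised.** Under Participants, inclusion requires "having completed ERCP", and one exclusion is "intraoperative conversion to open surgery due to major complications, such as perforation or severe bleeding", which is known only once the procedure is over. In Table 1 the "Randomization" tick stands in the after-surgery column, alongside the interventions. Randomization and Blinding describes sealed envelopes, "which the researcher will open before the intervention to access the allocation plan for each patient".

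**Analysis.** Data Analysis specifies Kaplan-Meier curves, log-rank tests and a Cox model for both primary outcomes under intention-to-treat. Each intervention is compared with routine care at .0167. It mentions neither late entry nor events before randomisation.

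**The concern.** The clock is already running in every child when the envelope is opened. The eligibility list does not ask whether the child has already passed gas or stool, so a child who has done so can be randomised and contribute a primary event. That event belongs to a period in which all four arms received the same care. It adds noise without signal, and a single hazard ratio then averages a stretch with no possible effect into the treatment effect.

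At stake is power. With about 18 children per arm and a threshold of .0167 there is little to spare. The reported hazard ratio would also understate what the interventions do once given.

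**Working it through.** **The plan's own figure.** For the omnibus F test with four groups, f = 0.593 and alpha .05, the noncentrality is N × f². At N = 52 it is 52 × 0.3516 = 18.3 (power .946). At N = 56 it is 56 × 0.3516 = 19.7 (power .962). So 56 is the smallest balanced total reaching .95. Then 56 / 0.8 = 70, which rounds up to 72 for four equal arms. The stated 56 and 72 reproduce. That calculation compares mean times and takes no account of events before randomisation.

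**Inputs for the check.** From the protocol: 18 per arm, two-sided alpha .05 / 3 = .0167, log-rank test. Assumed, because the documents do not give them: hazard ratio 3 acting only after randomisation, no censoring, the distribution of event times, and the gap.

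**Power by share of early events.** With a common gap and no censoring, the log-rank test uses only the order of events, so the early share and the hazard ratio determine power. The last column shows the spread over repeated simulations. One standard error at 2,500 runs is about √(.5 × .5 / 2,500) = .01.

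| Early share | Surgery clock, all events | Delayed entry | Spread over repeats |
|---|---|---|---|
| 0% | .75 | .75 | – |
| 2% | .72 | .74 | – |
| 5% | .67 | .70 | .66–.69 v .70–.73 |
| 10% | .59 | .68 | .59–.62 v .68–.71 |
| 20% | .44 | .60 | .44–.47 v .60–.62 |

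**From gap to early share.** For Weibull times with median m and shape k, the share before a gap L is 1 − 2^(−(L/m)^k). Two contrasting cases:

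| Case | Gap | Early share | Surgery clock v delayed entry | Hazard ratio seen (true 3) |
|---|---|---|---|---|
| m = 24 h, k = 2 | 2 h | 0.5% | .74 v .75 | 2.99 |
| | 4 h | 1.9% | .71 v .73 | 2.92 |
| | 6 h | 4.2% | .68 v .72 | 2.87 |
| m = 12 h, k = 1 | 2 h | 10.9% | .60 v .69 | 2.57 |
| | 4 h | 20.6% | .45 v .61 | 2.37 |
| | 6 h | 29.3% | .33 v .55 | 2.08 |

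For example, with m = 12, k = 1 and L = 4: 1 − 2^(−4/12) = .206.

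**Second model, with a gap that varies between children.** Times are normal with mean 24 h (assumed) and the protocol's SD of 13.03 h, truncated at zero. Treatment cuts the remaining time by 40%. Power is .745 v .753 for gaps of 0.5–3 h, .67 v .69 for 1–6 h, and .55 v .61 for 1–12 h. With gamma times of the same mean and SD it is .56 v .56, .49 v .49 and .35 v .38.

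**False positives.** With no treatment effect and 20% early events, the rejection rates were .022 (surgery clock) and .023 (delayed entry). Delayed entry therefore does not buy its power with extra type I error.

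**The case against.** The strongest reply is that nothing shows an early event will ever occur. The documents give no interval from ERCP to randomisation. If children are allocated promptly and first flatus typically comes around 24 hours, delayed entry gains almost nothing. This stands, and it makes the size conditional. A reader might infer that early events are in fact being counted and dilute every contrast. The documents support only that they can be counted. Defecation, if it comes later than flatus, is affected less.

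A reader might also infer bias in favour of the interventions. That does not follow. Randomisation balances early events in expectation, and they pull estimates towards no effect. Nor is surgery a wrong origin: it is clinically natural and can stay as the time scale.

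The first-session timing may be set in the intervention manual or the standard operating procedure, which are not shown, and survival coding is commonly left to an analysis plan. A prompt first session would shrink the problem. But the article itself fixes the origin, the order of events and the analysis, and together these admit early events.

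Delayed entry has its own difficulties. Assessments are four-hourly and need bowel sounds plus verbal confirmation, so an event before allocation may be documented only afterwards, on the word of a family that now knows the arm. Removing randomised children from a risk set also sits uneasily with the stated intention-to-treat analysis. Both objections shape the repair. Early status should be settled before the envelope is opened, and the all-randomised analysis should still be reported. Because the removal then rests on a fact that precedes randomisation, the randomised comparison is preserved.

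**Conclusion.** The point holds as a loss of efficiency of unknown size. The protocol lets flatus or stool that precedes randomisation count as a primary event, and no such event can respond to allocation. Under the assumed hazard ratio of 3, delayed entry gains about 2 points of power at 2% early events, 3 at 5%, 9 at 10% and 16 at 20%. With gaps up to 3 hours and times spread around 24 hours the loss is negligible. With a 12-hour median and a constant hazard, even a 2-hour gap costs about 9 points relative to delayed entry. The hazard ratio, event-time distribution and gap are all assumptions. The sequence of clock, eligibility and allocation is not. The change is worth making because it gave up no material power in any scenario tried and can still be fixed before outcome analysis: 38 of 72 children had been randomised by January 2026, with no interim analysis.

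**What to change.** 1. Record the clock time of randomisation in all four arms. Intervention session times cannot stand in for it, because conventional care has no sessions. For the 38 children already randomised, retrieve it from source records where available.
2. Immediately before the envelope is opened, record whether flatus and stool have each already occurred, so that reports made after allocation is known cannot decide it.
3. Keep time since surgery as the scale, but enter each child in the risk set at randomisation, separately for flatus and defecation. The R survival package already named in Data Analysis does this with `Surv(entry, time, event)`, and the log-rank comparison can be obtained as the score test of the Cox model.
4. Report by arm the time from ERCP to randomisation and the number of early events for each outcome. Give the all-randomised surgery-clock analysis as a sensitivity analysis.

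The cost is a few case report form fields and a short addition to Data Analysis, made before any outcome is compared by arm. A child with an early event leaves that outcome's risk set, and some entry times for children already enrolled may be missing or approximate. Delayed entry does not recover any wait between randomisation and first treatment, which properly remains part of the intention-to-treat effect. Study Design puts baseline assessment before randomisation and Data Collection and Management puts it after; the two should be reconciled, though neither moves randomisation ahead of ERCP.
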